### Trial design and setting

*Rationale*

WANTAIM is a cluster-randomised controlled crossover trial
^58^ being conducted in 10 clusters in PNG. We have adopted a cluster randomised trial design as our preferred option. Individual randomisation cannot be considered because it is neither logistically nor ethically feasible to randomly assign women to different types of care within the same clinic. In any case, the intervention cannot be blinded or compared with a placebo, so there is substantial potential for bias due to differential provision of care in the two arms, even if individual randomisation could be used.

A crossover design was chosen rather than a parallel cluster randomised trial design due to the considerable statistical efficiency of the former, and because this design provides an opportunity for all clusters to participate in the intervention arm at some point during the trial. In addition, this design will allow the health systems, health economics and acceptability components of the trial to be conducted in the same settings under different trial conditions (enabling direct ‘before / after’ comparisons to be made).

*Selection of trial clusters*

Trial clusters have been selected in consultation with provincial health authorities, church health services, health facility staff and other local stakeholders. Sites were selected based on antenatal clinic attendance data (e.g. average number of new attendees per week; total new attendees in previous 12 months; proportion of new attendees who met trial eligibility criteria); clinic staffing, experience and interest in participating in the trial; available clinical space and infrastructure (e.g. to enable point-of-care STI testing and treatment, ultrasound scans, and other trial procedures to be carried out); geographical location of health facility and catchment communities (in relation to other potential trial clusters); and previous experience in PNGIMR-led clinical and community-based research.

Each of the selected cluster health facilities has a designated weekday for new antenatal attendances, during which an average of 12–18 women attend their first antenatal visit. Site assessment visits indicated that around 70% of those attending would be eligible to participate in the WANTAIM trial. Assuming a high proportion (85%) of women who are eligible elect to participate, each site will enrol around 7–10 women per week and take 23–33 weeks to recruit the required sample size of 230 women per cluster in each phase of the trial.

*Intervention summary*

Women participating in the intervention arm of the trial will provide self-collected vaginal specimens for point-of-care STI testing (chlamydia, gonorrhoea, trichomonas and bacterial vaginosis), and will be provided with immediate treatment as indicated by their test results, at the following time points:

•   At enrolment (preferably before 20 weeks gestation);

•   One month after trial enrolment (to confirm that infections at enrolment have been cured and to detect incident infections. Women with a positive test result at this visit will be asked to return for repeat testing one month later);

•   At 34–36 weeks antenatal follow-up.

The rationale for this intervention schedule is based on:

a)   current scientific evidence which suggests that diagnosis and treatment of chlamydia, gonorrhoea, trichomonas and bacterial vaginosis early in pregnancy would have the greatest impact on low birth weight and preterm birth
^8,
31^;

b)   the lack of scientific evidence on the association between incident chlamydia, gonorrhoea, trichomonas and bacterial vaginosis in later pregnancy and risk of adverse birth outcomes, particularly preterm birth and premature rupture of membranes
^31,
40^.

To evaluate whether point-of-care testing in pregnancy increases the diagnosis and treatment of STIs compared with symptom-based syndromic management, residual urinalysis specimens collected at enrolment, after one month and at 34–36 weeks in the control arm of the trial will be retained and tested in batches. This will also enable the research team to provide appropriate antibiotic treatment at the postnatal visit, as indicated.

A summary of trial interventions and visits in
Figure 1 and a summary of trial procedures is provided in
Figure 2.

**Figure 1. f1:**
[figure not shown]
Summary of trial interventions and visits.

**Figure 2. f2:**
[figure not shown]
Summary of trial procedures.

### Randomisation

The unit of randomisation is a primary health care facility and its catchment communities. Ten geographically distinct clusters will be assigned in a 1:1 ratio to control and intervention arms in the first phase of the trial. Following a washout period of 2–3 months at the end of the first phase, each cluster will crossover to participate in the alternative trial arm in the second phase of the study (a so-called ‘A-B / B-A’ trial design). Randomisation will be stratified by province. In each province close to the start of recruitment, members of the local community advisory board, representatives from local health authorities, and staff from clinical research sites will be invited to a launch event in which the randomisation sequence will be selected by a senior independent stakeholder e.g. the Provincial Administrator. The Chief Investigator will prepare different randomisation sequences that will be put into separate identical opaque envelopes. These will be placed in a traditional woven string bag (a
*bilum*). The independent stakeholder will select one envelope from the
*bilum* and open it to reveal the final sequence to the audience.

A subgroup of up to 2000 newborns will be followed up at 1–2 weeks and 4–6 weeks postnatal to collect secondary outcome data (secondary objectives 7–9). Five of the 10 trial clusters will be randomly selected to participate in this part of the study. The randomisation sequence will be computer-generated and allocated by the trial statistician. Each of the clusters selected to participate in the extended postnatal follow-up component will do so during both the intervention and the control phase of the trial. Each selected cluster will thereby contribute around 200 newborns in each trial phase (2000 in total).

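### No restriction by crossover sequence is stated for the draw of the five neonatal follow-up clusters; a draw within sequence would guarantee a 3:2 split and protect the precision of secondary objective 7

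*Protocol article*

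**What the plan says.** The Randomisation section of the protocol article describes two separate random steps.

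- **Sequence allocation.** "Ten geographically distinct clusters will be assigned in a 1:1 ratio to control and intervention arms in the first phase of the trial", and after a washout "each cluster will crossover to participate in the alternative trial arm in the second phase of the study". A restriction is named for this step: "Randomisation will be stratified by province". The sequences are revealed at provincial launch events held near the start of recruitment.
- **Selection for extended neonatal follow-up.** "Five of the 10 trial clusters will be randomly selected to participate in this part of the study". On method the section adds: "The randomisation sequence will be computer-generated and allocated by the trial statistician". No stratification or other restriction is named for this step, and its timing relative to the launch events is not given. On participation: "Each of the clusters selected to participate in the extended postnatal follow-up component will do so during both the intervention and the control phase".

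The selected clusters supply the data for secondary objectives 7 to 9. Under Trial aim and objectives, objective 7 (neonatal eye infection and/or pneumonia) is worded as a comparison with standard antenatal care. Objective 8 (mother-to-child transmission) is not worded as an arm comparison, and objective 9 concerns diagnostic accuracy. Statistical analysis commits all analyses to methods that reflect the cluster crossover design.

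**The concern.** In a two-period cluster crossover, using both phases of each cluster removes differences between clusters. It does not remove differences between phases. Treatment and period effects are separated only because some clusters run in one order and some in the other.

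All ten clusters together are balanced by design. A subset of five need not be, and with five clusters the mix of sequences can become poor. At 4:1 a single cluster represents one whole sequence and carries half the weight of the period-adjusted estimate. The Sample size section itself allows for one or more clusters failing to complete. If that lone cluster failed, the remaining 4:0 would leave treatment inseparable from period. At 3:2, losing any one cluster still leaves both sequences represented.

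Period effects are plausible for objective 7. By the article's figures, recruitment takes 23 to 33 weeks per phase (about 5.3 to 7.6 months) and the washout lasts 2 to 3 months. A cluster's second phase therefore starts roughly 7 to 11 months after its first. Respiratory illness may differ between those times, although the article gives no figure for this.

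**Working it through.** **Inputs**

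- 10 clusters, 1:1 by sequence (Randomisation). I take this as 5 and 5. That is an assumption, because the number of provinces and the split within each are not given.
- 5 clusters drawn, both phases used, about 200 newborns per cluster per phase (Randomisation).

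**Check of the plan's own figure.** 5 clusters × 2 phases × 200 = 2000 newborns, as stated. The article gives no probability for the split by sequence.

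**Chance of each split under a simple draw.** P(j from the first sequence) = C(5,j) × C(5,5−j) / C(10,5), with C(10,5) = 252.

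| Split (either way) | Draws | Probability |
|---|---|---|
| 3:2 | 2 × 10 × 10 = 200 | 79.4% |
| 4:1 | 2 × 5 × 5 = 50 | 19.8% |
| 5:0 | 2 × 1 × 1 = 2 | 0.8% |

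**Precision.** Let d be the change in a cluster's outcome from phase 1 to phase 2. Its mean is period plus treatment in one sequence and period minus treatment in the other. The period-adjusted treatment effect is half the difference between the two sequence means of d. With clusters of similar size its variance is proportional to (1/n1 + 1/n2)/4.

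- 3:2: (1/3 + 1/2)/4 = 0.208
- 4:1: (1/4 + 1)/4 = 0.3125
- Ratio: 0.3125/0.208 = 1.50, and √1.50 = 1.22, so the standard error is 22% wider.
- 5:0: one sequence is empty, so the effect cannot be estimated.

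**Average over the 250 estimable draws.** The mean of 1/n1 + 1/n2 is (200 × 0.833 + 50 × 1.25)/250 = 0.917, against 0.833 for a guaranteed 3:2. The ratio is 1.10: 10% more variance, or about a 5% wider standard error.

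**If period were not modelled.** The share of a period effect carried into a crude arm comparison is |n1 − n2|/5: 20% at 3:2, 60% at 4:1 and 100% at 5:0.

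**Sensitivity to the 5:5 assumption.** The total chance of 4:1 or 5:0 is 52/252 = 20.6% at 5:5. It would be 28.6% if the sequences split 4:6. If the five clusters were drawn within provinces but without regard to sequence, illustrative layouts give 22% to 37.5%.

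**The case against.** The strongest objection is that the article is silent rather than wrong. A draw stratified by sequence is also random and computer-generated, so it would fit the text. The full protocol and the analysis plan are not shown and may specify one. This stands in part: a reader might infer that sequence was ignored, but the text shows only that no restriction is stated. A simple draw remains the natural reading, because the same section does name a ratio and a stratification factor for the sequence allocation.

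A reader might also add the two bad splits together and infer a 1-in-5 risk of a confounded comparison. The documents do not support that. Of the 20.6%, 19.8 points are 4:1 splits. Every selected cluster supplies both arms, so a 4:1 split costs precision without biasing a period-adjusted analysis. Complete confounding arises in 2 of 252 draws.

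The scope is also narrow. Objective 7 is the only subset objective worded as an arm comparison, objective 9 does not depend on sequence balance, and the primary outcome uses all ten clusters.

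The seasonal mechanism is not quantified either. Launches are held province by province and recruitment is expected to take about three years, so phases need not fall in the same season across clusters. That limits how large a common period effect may be, but does not remove the precision argument.

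**Conclusion.** The point holds as a minor design improvement. Assuming a simple draw and a 5:5 division of sequences, there is a 19.8% chance of a 4:1 split, with 1.5 times the variance and a 22% wider standard error than 3:2, and a 0.8% chance of a non-estimable 5:0 split. The average cost over estimable draws is modest, at about 10% in variance. It falls mainly on objective 7. The precision figures assume that period is adjusted for, which is consistent with the article's commitment to methods suited to the crossover design. They also assume clusters of similar size. The documents do not show that the draw actually made was unrestricted or unbalanced.

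**What to change.** State in the Randomisation section that the five clusters are drawn within sequence: three from one and two from the other, with the sequence that gives three chosen at random. The chance of 4:1 or 5:0 then falls to zero. Exact balance is impossible with five clusters, so 3:2 is the best that can be had. If a restricted draw was already used, one sentence saying so settles the point.

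If an unrestricted draw has already been made (the article reports that recruitment began in July 2017), report the split by sequence and include a period term in the analysis of outcome 7.

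The change needs no more clusters or newborns. Its one small cost is timing: the draw must follow the provincial launch events, or be planned within the sequences prepared for them, so that the sequences are known or provided for when the five clusters are chosen.

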### Study participants and eligibility criteria

Women aged 16 years or over, attending antenatal clinic at 26 weeks gestation or below (confirmed by obstetric ultrasound scan at first antenatal clinic visit), living within approximately one hour’s drive of a participating study clinic, and able to provide reliable contact details to facilitate future community tracing and postnatal follow-up, are eligible to join the study. Women found to be severely anaemic at enrolment (haemoglobin less than 6.0 g/dl accompanied by symptoms), or those with a permanent disability that prevents or impedes study participation and/or comprehension (such that it is not possible to obtain informed consent to participate), are excluded from participation in the trial. All those excluded on health grounds will be referred to the appropriate clinical specialist at each site, where they will be managed according to PNG national treatment guidelines
^59^.

### Field team

Overall responsibility for the conduct and management of the trial will rest with the Chief Investigators. The study will be managed on a day-to-day basis by an experienced Trial Coordinator based at the PNGIMR who will oversee the trial at all sites and supervise a dedicated field team comprising clinical, laboratory, data management, community liaison and administrative support staff. Clinical research staff will be qualified nurses and/or midwives, and will be responsible for the conduct of trial-related procedures and the provision of routine antenatal services for women participating in the trial.

### Recruitment and informed consent

Immediately prior to the start of enrolment at each site, potential participants will be notified that the trial is about to start through community meetings (e.g. at markets, after church), local media (e.g. broadcasts in PNG Pidgin [one of three official national languages in PNG], and local languages), and other mobilisation activities as advised by local stakeholders. Activities will be conducted by clinical research staff and members of the study community liaison team. On arrival at participating antenatal clinics, women will be provided with general information about the trial though a 5–10-minute group talk provided by a member of the clinical research team using a pictorial flipchart. Women who express an interest in taking part in the trial will be given a copy of the study Participant Information Sheet (available on Open Science Framework
^60^) to read whilst waiting.

All participants will be required to complete written informed consent procedures prior to trial enrolment. All information and consent procedures will be conducted in PNG Pidgin or English, as preferred by the individual participant. In accordance with ICH Good Clinical Practice guidelines (ICH GCP), participants unable to read and/or write will be required to have an impartial witness present during the above procedures.

### Enrolment visit procedures

Women attending routine antenatal clinics in both the control and intervention arms of the trial will receive standard antenatal care in accordance with PNG national guidelines
^59^. All women will be advised to return for a minimum of three additional antenatal clinic visits, in accordance with national and WHO recommendations; and to attend a health facility to give birth.

*Procedures at enrolment: control clusters*

a) The following routine antenatal clinic procedures will be conducted
^59^:

○ A face-to-face clinical interview conducted in the most appropriate language (e.g. English or PNG Pidgin) to collect baseline antenatal data, including current and past obstetric history.

○ A general medical and obstetric examination, in which the following will be recorded: general health and well-being; signs of anaemia or other systemic disease (e.g. tuberculosis); weight and height; blood pressure; fundal height and foetal heart rate.

○ Provider initiated counselling and testing for HIV (PICT) and syphilis infection, as per PNG national guidelines.

○ Collection of specimens for routine on-site testing: haemoglobin (Hb) estimation; rapid diagnostic test (RDT) for malaria (if symptomatic e.g. fever); collection of a midstream urine specimen for urinalysis (protein and glucose testing).

○ Women will be provided with routine antenatal care as per PNG national guidelines, including sulphadoxine-pyrimethamine for malaria prevention; iron and folate supplementation; tetanus toxoid immunization; treatment for syphilis if required; and STI syndromic management for women presenting with genital symptoms, as per PNG national guidelines.

○ Women with a positive RDT for malaria will be given malaria treatment in accordance with PNG national treatment guidelines.

○ Women who test positive for HIV infection will be referred for specialist review and initiation of antiretroviral therapy.

b) The following study-specific procedures will be conducted:

○ Collection of additional clinical, behavioural and socio-economic and demographic information, including risk factors for low birth weight and preterm birth (e.g. smoking, alcohol and betel nut consumption; recent or current systemic illness, e.g. malaria or tuberculosis; poor maternal nutritional status, e.g. mid-upper arm circumference <22 cm)
^61–
63^

○ A trans-abdominal obstetric ultrasound examination to measure biparietal diameter (BPD), head circumference (HC), femoral length (FL) and abdominal circumference (AC), to estimate gestational age, as specified in study-specific standard operating procedures.

○ Storage of residual urine specimen for off-site STI PCR testing to be conducted in batches in order to obtain information on the prevalence of curable STIs (
*C. trachomatis, N. gonorrhoeae, T. vaginalis* and bacterial vaginosis) among women participating in the control arm. Urine remaining after off-site STI testing will be retained for future laboratory testing with participants’ written consent.

○ Women with a positive urine test result will be counselled regarding their diagnosis and provided with treatment for them and their partner at the first postnatal visit conducted within 72 hours of birth.

○ A dried blood spot (DBS) will be collected and stored for later off-site malaria quantitative real-time PCR (qPCR) testing.

○ Information will be recorded in a study-specific Enrolment Case Report Form (CRF) at the time the measurements and interview are conducted.

○ A summary of key clinical findings will also be recorded in the participant’s Health Record Book that will be checked to see if any visits to a health centre have been documented. If the participant has any record of such a visit, the field study team will record the date of the most recent visit and any medication the participant received in the Enrolment CRF.

○ At the end of the Enrolment visit, a short interview with a dedicated community volunteer will be conducted in order to collect home address and other locator information to facilitate future community tracing and postnatal follow-up. A separate Locator Form will be used to record this information and will be securely stored in a different location to completed Enrolment CRFs.

*Procedures at enrolment: intervention clusters*

Enrolment procedures in intervention clusters will be identical to those in control clusters, with the following exceptions:

○ Women will provide two self-collected vaginal swabs for same-day, point-of-care testing at the study health centre:

a) one swab will be tested for chlamydia, gonorrhoea and trichomonas using the GeneXpert platform; andb) one swab will be tesed for bacterial vaginosis, using the BVBlue Test.

○ Clinic staff will use a laminated pictorial guide to help them explain the correct way to collect vaginal specimens for STI testing. During the explanation, staff will indicate how samples are to be collected using a specimen collection kit reserved for this purpose, and will encourage women to handle the swabs and to review the pictorial guide themselves.

○ When staff are satisfied that the participant understands the collection procedure, she will be asked to collect her specimens in a private room or the clinic toilet. This approach has been successfully used in our earlier research and found to be acceptable to both study participants and clinic staff.

○ Women who have a positive STI test result will be provided with immediate, directly observed treatment in accordance with PNG national guidelines for the management of STIs. Women will also be counselled regarding the importance of providing STI treatment for their husband/partner in order to prevent re-infection, and the most appropriate options for ensuring successful partner treatment (e.g. same-day treatment if accompanied by their partner; provision of a partner treatment pack; return for couple counselling and treatment).

○ Only those with a positive STI test result will be treated. STI syndromic management will only be provided for vulvovaginitis considered on clinical features due to candidiasis, for which additional treatment will be provided as per national guidelines (e.g. nystatin pessaries and/or clotrimazole cream)
^59^.

○ If the test result on any of the above assays is invalid, women will be asked to provide an additional self-collected swab and given further counselling on self-collection, to allow repeat testing on the same day in the clinic.

○ Residual fluid remaining in the GeneXpert sample processing tube will be retained for future laboratory testing with participants’ written consent.

○ Urinalysis will be conducted as per routine antenatal care (e.g. for protein and glucose) but residual urine will not be stored in intervention clusters.

### Procedures during antenatal follow-up

Following enrolment, women in both the control and intervention arms of the trial will receive standard routine antenatal care and will be asked to re-attend for a minimum of three further antenatal clinic visits, in accordance with national guidelines:

1) The first antenatal follow-up visit will be conducted approximately four weeks after trial enrolment;

2) The second antenatal follow-up visit will be conducted approximately eight weeks after trial enrolment;

3) The third antenatal follow-up visit will be conducted in the third trimester at approximately 34–36 weeks gestation.

*Procedures during antenatal follow-up: control clusters*

○ A general medical and obstetric examination, and conduct of routine antenatal investigations: haemoglobin estimation; RDT for malaria (if clinically indicated); collection of a midstream urine specimen for urinalysis (protein and glucose testing).

○ In addition to routine antenatal care, a short face-to-face interview will be conducted at all visits to obtain information on risk factors for low birth weight/preterm birth (e.g. smoking, alcohol and betel nut use) and potential confounders (e.g. care-seeking, sexual behavioural data, condom use, concomitant antibiotic use for other non-genital infections).

○ Information will be recorded in study-specific CRFs at the time the measurements and interview are conducted.

○ Participants will be provided with health information at all visits, particularly the importance of having a supervised birth in a health facility, and reminded of the importance of informing the research team within 24 hours of giving birth if they have been unable to give birth at their local health facility.

○ All those who present with symptoms suggestive of a genital STI will be treated according to national syndromic management guidelines.

○ At follow-up visits #1 and #3, a urine specimen will be collected and stored for off-site STI testing to be conducted in batches in order to obtain information on the prevalence of curable genital STIs among women participating in the control arm. Women who test positive for these infections (and their partners) will be provided appropriate treatment at their first postnatal visit.

*Procedures during antenatal follow-up: intervention clusters*

○ Follow-up procedures in intervention clusters will be identical to those in control clusters with the exception that at follow-up visits #1 and #3, women will be asked to provide two self-collected vaginal swabs that will be tested as per the enrolment visit. Women who have a positive STI test result provided with same-day treatment in the clinic.

